**Figure 3 fig-3:**
[figure not shown]
Flowchart for assessing physical activity.

### Other parameters

To explain the baseline characteristics of the patients, we will investigate information on sex, age, drinking history, smoking history, site of coronary artery stenosis, Killip classification, contrast agent dose, medical history, complications, length of hospital stay, height, and weight from the electronic medical record at the time of registration. Moreover, we will investigate the left ventricular ejection fraction evaluated by echocardiography at the time of discharge.

### Statistical analysis

In this study, the analysis will involve an intention to treat analysis. Therefore, patients’ consent will be obtained to use 3-month post-assessment information derived from the observed clinical data in the event of dropout or poor adherence in the intervention arm. Regarding background information of participants, discrete data, including frequencies, proportions, and 95% confidence intervals, will be calculated for each group. For continuous data, the mean, standard deviation, and 95% confidence interval will be calculated for each group.

The primary outcome, eGFRcys, will be examined using analysis of covariance (ANCOVA), with adjustment for baseline values as covariates for the least squares mean of eGFRcys at 3 months. Secondarily, between-group comparisons of the change in eGFRcys will be performed in the same way.

The secondary endpoints of ACR, BNP, average number of steps, peak VO2, and EQ-5D will be analyzed using ANCOVA, with adjustment for baseline values. Between-group comparisons of the incidence of adverse events will be performed using the *χ*-square test.

All statistical analyses will be performed using SPSS version 29.0 (IBM Corp., Armonk, NY, USA). Statistical significance will be set at an alpha-level of 0.05.

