### Randomization and blinding

Randomization allocation will be performed on the web using the UMIN INDICE cloud (https://www.umin.ac.jp/indice/cloud.html). Allocation will be completed within 2 weeks of initiation of inpatient CR. This study will not be blinded. Adjustment factors for allocation will be age (<60 years *vs.* ≥60 years), sex (male *vs.* female), and highest creatine kinase level (<3,000 U/L *vs.* >3,000 U/L).

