### Sample size calculation

To determine the impact of online PA management support on eGFRcys, we will examine between-group differences in eGFRcys. Since there have been no reports of a clinically meaningful minimum difference in eGFRcys among patients with ACS, we arbitrarily assumed that the between-group difference in eGFRcys after 3 months would be five mL/min/1.73 m^2^. If the standard deviation of eGFRcys in both groups is set to be 16.0 in reference to our previous study (Sato et al., 2019), the effect size was 0.3125.

Subsequently, assuming that between-group comparisons of eGFRcys after 3 months would be performed using ANCOVA with baseline values as covariates, G*Power 3.1 was used to calculate the required sample size with an effect size *f* = 0.3125, alpha = 0.05, and power = 0.8. The results showed that 83 cases were detected. Accordingly, we calculated that the required sample size was 83 cases, and the target number of cases was set at 88 (44 in the intervention group and 44 in the control group), taking into account the possibility of dropouts (5%) in both groups.

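### Allocation is balanced on age, sex and peak creatine kinase, but the stated primary ANCOVA adjusts only for baseline eGFRcys; if those factors predict outcome beyond baseline, the test is somewhat conservative

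*Protocol article*

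**What the plan says.** In the protocol article, Randomization and blinding lists what allocation is balanced on: "Adjustment factors for allocation will be age (<60 years *vs.* ≥60 years), sex (male *vs.* female), and highest creatine kinase level", the last split at 3,000 U/L. It does not say whether this is done by stratified blocks or by minimisation.

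Statistical analysis gives the primary model as an ANCOVA "with adjustment for baseline values as covariates for the least squares mean of eGFRcys at 3 months". The secondary endpoints ACR, BNP, step count, peak VO2 and EQ-5D are also analysed by ANCOVA adjusted for baseline values.

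Sample size calculation rests on the same model: "assuming that between-group comparisons of eGFRcys after 3 months would be performed using ANCOVA with baseline values as covariates". The abstract and Outcome assessment also describe 3-month eGFRcys adjusted for baseline. No section puts an allocation factor into a model.

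**The concern.** Balancing the arms on a prognostic factor removes most of that factor's contribution to the chance difference between the arms. A model that omits the factor still counts its contribution as residual variance. The reported standard error then exceeds the real variability of the treatment estimate, confidence intervals are too wide, and the test rejects less often than its nominal level.

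The sponsor's choice of these three factors for balancing suggests that they are thought prognostic. Using them in allocation but not in analysis gives up precision that the randomisation has already provided, in a trial of 88 patients. How much is given up depends on how far the factors predict 3-month eGFRcys once baseline eGFRcys is in the model.

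**Working it through.** **Inputs from the documents (Sample size calculation).** Difference: "we arbitrarily assumed that the between-group difference in eGFRcys after 3 months would be five mL/min/1.73 m^2". SD: "If the standard deviation of eGFRcys in both groups is set to be 16.0". Settings: "effect size *f* = 0.3125, alpha = 0.05, and power = 0.8". Target: "the target number of cases was set at 88 (44 in the intervention group and 44 in the control group", after 5% dropout.

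**Assumed inputs.** The partial R² of the three factors given baseline eGFRcys is not in the documents; a range of 0 to 0.20 is used. The simulation also assumes factor prevalences of 0.70, 0.20 and 0.35, equal shares of R² across the factors, and factors independent of baseline.

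**Step 1: reproduce the plan's figure.** With f = 5/16 = 0.3125, the ANCOVA F test has 1 and N − 2 − c degrees of freedom (c covariates) and noncentrality f²N.

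- N = 83, c = 1: noncentrality 0.3125² × 83 = 8.105, with 1 and 80 df; power 0.803.
- N = 82, c = 1: power 0.798, so 83 is the smallest N that reaches 80%.
- Dropout: 83/0.95 = 87.4, rounded up to 88.

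The stated 83 and 88 reproduce. With four covariates (baseline plus three binary factors) and R² = 0, power at N = 83 is still 0.803 and the required N is still 83.

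**Step 2: power with the factors in the model, by formula.** Adding the factors divides the residual variance by 1/(1 − R²), so f becomes f/√(1 − R²), with c = 4 and 77 denominator df at N = 83.

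| Assumed partial R² | SE without factors / SE with factors, 1/√(1 − R²) | Power with factors, N = 83 | N for 80% power |
|---|---|---|---|
| 0 | 1.00 | 0.803 | 83 |
| 0.02 | 1.01 | 0.811 | 81 |
| 0.05 | 1.03 | 0.822 | 79 |
| 0.10 | 1.05 | 0.842 | 75 |
| 0.20 | 1.12 | 0.882 | 67 |

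Setting these against 0.803 slightly overstates the loss, because balanced allocation by itself already helps the baseline-only test a little. Step 3 allows for that.

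**Step 3: simulation of both models on the same data.** Stratified permuted blocks of four in the eight cells, N = 84, 12,000 runs per setting, and a true difference of 2f = 0.625 residual SDs for power.

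| Assumed partial R² | Baseline-only: mean model SE / true SD of estimate | Baseline-only: type I error | Baseline-only: power | With factors: type I error | With factors: power | Power given up (points) |
|---|---|---|---|---|---|---|
| 0 | 0.2190/0.2181 = 1.00 | 0.046 | 0.804 | 0.046 | 0.800 | none (adding costs about 0.4) |
| 0.05 | 0.2190/0.2163 = 1.01 | 0.047 | 0.806 | 0.052 | 0.818 | 1.2 |
| 0.10 | 0.2191/0.2080 = 1.05 | 0.038 | 0.811 | 0.048 | 0.838 | 2.7 |
| 0.20 | 0.2192/0.2009 = 1.09 | 0.033 | 0.823 | 0.053 | 0.879 | 5.6 |

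The Monte Carlo standard error of a 5% rejection rate is √(0.05 × 0.95/12,000) = 0.002. The 0.046 at R² = 0 is therefore noise around 0.05, and 0.047 at R² = 0.05 cannot be told from it. The conservatism shows clearly only from R² = 0.10 upwards. A smaller stratified run gave 0.830 against 0.880 at R² = 0.20, a loss of 5.0 points. A smaller run with minimisation pointed the same way wherever R² was not negligible.

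**The case against.** The strongest reply is that nothing is contradicted. The abstract, Outcome assessment, Statistical analysis and Sample size calculation all describe the same baseline-adjusted model, and the sample size assumed exactly that. This stands. A reader might infer that the omission undercuts the planned 80% power, biases the estimate or endangers the type I error; the documents and the calculation support none of these. The loss is relative to a better available model.

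A reader might also infer that the standard error is certainly too large and power certainly lost. That is not supported either, since at R² = 0 there is no loss. The documents point to the low end: age and sex are terms of the eGFRcys equation in Outcome assessment, so baseline carries part of them. Baseline is also taken about two weeks after onset, so an early renal effect of infarct size may already be partly in the covariate.

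Nor can it be said that the arms cannot differ on these factors. The allocation method is not given, minimisation balances margins only, and eight cells among 88 patients leave room for residual imbalance.

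A covariate list might be left to a separate analysis plan. Here, however, the primary model is stated and the sample size is built on it, so the point concerns a model that is fixed in the text. Reading baseline values as including the allocation factors is not plausible: the same phrase serves each endpoint's own baseline, and peak creatine kinase appears neither in Table 2 nor under Other parameters.

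The argument does not extend to hospital. Hospital is not among the stated allocation factors, and no calculation here supports adding it.

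**Conclusion.** The point holds in conditional form. The stated analysis leaves out the factors on which allocation is balanced. To the extent that they predict 3-month eGFRcys beyond baseline, its standard error is too large and its test conservative. Over the assumed R² range, the cost runs from nothing to 5 to 6 points of power on the plan's own f, and is probably near the lower end.

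The points are measured at the plan's f = 0.3125. That value is 5/16, a standardised mean difference, and for two equal groups f would be half of it; this is a separate matter. Taking f = 0.15625 with an assumed baseline correlation of 0.7, the Step 2 formula gives power at N = 83 of 0.504 without the factors and 0.524, 0.546 and 0.595 with them at R² of 0.05, 0.10 and 0.20. The gain stays modest at low R².

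This is a worthwhile improvement to the analysis. It is not a threat to the trial's validity.

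**What to change.** In Statistical analysis, state the primary model as: 3-month eGFRcys = arm + baseline eGFRcys + age + sex + peak creatine kinase category. Add the same three allocation factors to each secondary ANCOVA, next to that endpoint's own baseline value. Use the creatine kinase category as recorded at allocation, and say where a value of exactly 3,000 U/L falls, since the text covers only values below and above it. Settle this before outcome data are examined, which also closes off later choice of covariates in an open-label trial.

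The cost is one or two sentences and three degrees of freedom out of about 80 (80 to 77 at N = 83). If the factors predict nothing, at most about 0.4 points of power are lost. The required N stays at 83, and no new data are needed because the factors must be known for allocation.

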### Online support for PA management

Patients in the intervention group will receive a wrist-worn wearable device (Fitbit Inspire 3, Fitbit, Inc, San Francisco, CA, USA) after assignment, and a web application (Recaval, SapplyM, Inc., Tokyo, Japan) for PA management will be downloaded to their smartphones. Data regarding PA and pulse rate obtained from the wearable device will be transmitted in real time *via* the application to the tablet device of the physical therapist in charge of the research facility. The wearable device is designed to locally store data until an internet connection is available. In addition to this biometric monitoring, the web application has chat and report feedback functions that allow two-way communication between patients and medical professionals. Patients will be instructed to wear the wearable device unless they are bathing or charging the device. Moreover, patients will be instructed to enter their daily blood pressure and self-records of subjective symptoms into the application, which will also be monitored daily by the physical therapist. Using this web application, patient information is completely anonymized; each patient is assigned a specific ID. In addition, this web application has a robust access restriction function. Only the interventionists at each research facility are only given access to the patient data of their own institution and have no access to the patient data of other research institutions.

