### Usual care

All patients in both groups will receive usual care, including patient education, medications, outpatient visits, and laboratory tests upon discharge, within the relevant scope. However, if patients wish to participate in outpatient CR during the observation period, their wishes will be respected, and they will be allowed to participate in outpatient CR after consultation with their physician. In this case, the patient will not be excluded from the study and will continue to receive “intervention and outpatient CR” in the intervention group and “usual care and outpatient CR” in the control group.

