**Medication**		
**Adverse events**		
(Intervention group only) ** Fitbit data:** daily sleep time and heart rate (maximum, minimum, and average)		

Secondary outcomes will include the urine albumin/creatinine ratio (ACR), BNP, average step count, peak oxygen uptake (VO2) based on a symptom-limited cardiopulmonary exercise test (CPET), Euro QOL 5-dimensions 5-levels, and incidence of adverse events. In addition, blood biochemical analysis data such as urea nitrogen; albumin; triglycerides; high- and low-density cholesterol; hemoglobin; and blood glucose will be collected. These outcome measures will be assessed concurrently with the primary evaluation. In the symptom-limited CPET, to avoid overloading the cardiovascular system after ACS, the exercise load is terminated when the gas exchange ratio reaches 1.2, which is defined as the peak point, even before reaching the symptom limit (Sato et al., 2023).

PA assessment will be performed immediately after discharge and after 3 months for a 7-day period. The Active Style Pro HJA-750 (Omron Healthcare Company; Kyoto, Japan), which has a 3-axis accelerometer that has been validated and shown to be highly reliable (Oshima et al., 2010; Ohkawara et al., 2011), will be used to evaluate PA and the average number of steps. Sedentary behavior, light-intensity PA, moderate-intensity PA, and vigorous-intensity PA will be defined as PA of ≤1.5 metabolic equivalents (METs), >1.5 and <3.0 METs, ≥3.0 and <6.0 METs, and >6.0 METs, respectively (Bull et al., 2020); moreover, the time spent wearing the device will be collected. To avoid the impact of checking PA on increasing PA levels, the researcher sets the device to prevent displaying the PA data. The patients will be instructed to wear the accelerometer at all times except when sleeping and bathing. If the time the device is worn is <10 h per day, activity data for that day will be excluded. The minimum number of days required for evaluation is defined as “4 days or more”, which is more than half of the 7 days (Fig. 3). Patients will return the accelerometer to the hospital by mail at the end of that 7-day PA measurement period. The principal investigator at each hospital will transfer PA data from the accelerometer to the computer *via* a reader (HHX-IT4, Omron Healthcare Company; Kyoto, Japan).

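### The between-arm test of adverse-event incidence is open to differential ascertainment, mainly of symptomatic and non-serious events, because only the intervention arm is monitored daily through the app

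*Protocol article*

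**What the plan says.** The last paragraph of the Outcome assessment section that lists secondary outcomes ends that list with "and incidence of adverse events". On timing it adds: "These outcome measures will be assessed concurrently with the primary evaluation". The primary evaluation is at baseline (discharge) and 3 months, with no restriction to one arm.

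The Statistical analysis section fixes the test: "Between-group comparisons of the incidence of adverse events will be performed using the" chi-square test. The significance level is common to all analyses: "Statistical significance will be set at an alpha-level of 0.05". The comparison is not limited to serious events or to events collected in a particular way.

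Contact between assessments differs by arm. Under Online support for PA management, "Patients in the intervention group will receive a wrist-worn wearable device" and the linked web application. These patients are asked to "enter their daily blood pressure and self-records of subjective symptoms into the application, which will also be monitored daily by the physical therapist". The same section goes on to list triggers for a therapist's status check by chat, including worsening chest pain, breathlessness or fatigue in the self-records. Telephone or video interviews are added where needed.

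For the control arm, the Usual care section gives what both groups share: "All patients in both groups will receive usual care, including patient education, medications, outpatient visits, and laboratory tests upon discharge". No symptom diary or daily review is described for controls. The Randomization and blinding section says the study is not blinded.

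**The concern.** Part of the intervention works as a system for noticing symptoms and abnormal readings. A brief dizzy spell, a low blood pressure reading or a few days of muscle pain is likely to leave a dated record in the intervention arm. In the control arm the same event depends on the patient recalling it at a visit or on someone having charted it. If such records enter the adverse-event count, the test compares a mixture of event occurrence and event detection.

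Two misreadings could follow. With equal true incidence, the intervention could appear to cause more events. With a true excess, readers could dismiss it as closer observation, and the data would not settle the matter. The secondary objectives include whether this support can be an alternative for patients who have difficulty attending outpatient rehabilitation, and the safety comparison bears directly on that.

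**Working it through.** **1. Does the article fix the source of the adverse-event count?**

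| Point | Intervention arm | Control arm |
|---|---|---|
| Assessment at baseline and 3 months | Yes | Yes |
| Usual outpatient visits | Yes | Yes |
| Daily symptom and blood pressure entry | Yes | Not described |
| Daily therapist review | Yes | Not described |
| Contact triggered by worsening symptoms | Yes | Not described |
| App records stated to count as adverse events | Not stated | Not applicable |
| App records stated to be excluded | Not stated | Not applicable |

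The asymmetry in contact is stated. Whether it reaches the count is left open in both directions.

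**2. How large could the effect be?**

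The article gives no figure for adverse events, so there is none to reproduce. Inputs:

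- Arm size: 44 and 44, from Sample size calculation.
- Level: 0.05, from Statistical analysis.
- True incidence p, equal in both arms: 20% or 40% (assumption).
- Detection in the intervention arm: 90% (assumption).
- Detection in the control arm: 50-80% (assumption), with 90% as the reference case.

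Observed incidence is p × detection. For p = 40%, the intervention arm shows 0.40 × 0.90 = 0.36. The control arm shows 0.40 × 0.80 = 0.32 down to 0.40 × 0.50 = 0.20. For p = 20%, the figures are 0.18 against 0.16 down to 0.10.

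With a and b events among n = 44 per arm and m = a + b, the uncorrected Pearson statistic is

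X² = 2n · (n·|a − b|)² / [n² · m · (2n − m)],

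and the test rejects when X² > 3.841. The rejection probability is the sum, over all pairs (a, b) that reject, of the product of the two binomial probabilities. This is exact enumeration with no simulation error.

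| True incidence | Control detection | Observed rates | Probability of rejection |
|---|---|---|---|
| 40% | 90% (equal) | 0.36 vs 0.36 | 5.5% |
| 40% | 80% | 0.36 vs 0.32 | 7.3% |
| 40% | 70% | 0.36 vs 0.28 | 13.3% |
| 40% | 60% | 0.36 vs 0.24 | 24.0% |
| 40% | 50% | 0.36 vs 0.20 | 39.8% |
| 20% | 90% (equal) | 0.18 vs 0.18 | 5.4% |
| 20% | 80% | 0.18 vs 0.16 | 6.1% |
| 20% | 70% | 0.18 vs 0.14 | 8.5% |
| 20% | 60% | 0.18 vs 0.12 | 12.9% |
| 20% | 50% | 0.18 vs 0.10 | 20.0% |

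**3. Direction.** The excess rejections are one-sided. At a control detection of 70% or lower, at least 91% of all rejections show more events in the intervention arm. At 80%, the share is 76% (p = 20%) to 86% (p = 40%).

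**4. Sensitivity to the form of the test.** A continuity-corrected chi-square is conservative at this sample size. For 0.18 vs 0.14 it rejects in 3.9% of trials, below the nominal level. For 0.36 vs 0.20 it still rejects in 29.8%.

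**The case against.** The strongest reply is that the link from app to adverse-event count is inferred. Daily monitoring is described as a way to deliver and safeguard the intervention, and the Outcome assessment section gives both arms a common assessment time. On its natural reading, part of the remedy is already planned. Collection details may also sit in the full protocol, which is not shown, and their absence from an article is no fault. This stands as far as it goes: one cannot say that events will be recorded unequally, only that they may be. It does not close the point. A common assessment time does not exclude events already known from the app, and the test as worded has no limit to events collected in the same way.

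A reader might infer more: that the test measures detection and not safety, and that the endpoint cannot be interpreted. The article does not support this. Deaths and hospitalisations would probably be found in either arm. Control patients have outpatient visits and the 3-month study assessment, and patients unable to attend regular visits are excluded. Nor can Table 1 be read as a list of adverse events recorded in one arm only. It sets criteria for discontinuing the intervention and does not define adverse events.

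Finally, the size rests entirely on assumed values. A gap of 90% against 80% raises the rejection rate only to 6.1-7.3%. That is correct, and it limits how firmly the point can be put.

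**Conclusion.** The point holds as a plausible, directional bias in one secondary endpoint. The unequal surveillance, the lack of blinding and the unrestricted between-arm test are all stated. That app-detected events enter the count is possible and not excluded, but it is not stated. The bias would concern mainly symptomatic and non-serious events and would tend to make the intervention look less safe.

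Under equal true incidence of 20-40%, detection of 90% against 50-80%, 44 per arm and an uncorrected test, false-positive rates run from about 6% to about 40%, against about 5% with equal detection. None of these incidence or detection values comes from the article, so the range shows what could happen and does not estimate what will. The primary analysis of eGFRcys is not affected. This is a cheap improvement, not a flaw that undermines the trial.

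**What to change.** State in the Statistical analysis section that the between-arm test covers only events ascertained identically in both arms: deaths, hospitalisations, cardiovascular events, and events found by the same enquiry and the same chart review at the 3-month assessment. Report events detected only through the app, chat or therapist review descriptively, for the intervention arm alone. If the full protocol already defines the source in this way, one sentence in the analysis text saying so is enough.

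The cost is a change of analysis wording and one question sheet used in both arms at a visit that already takes place. The downside is that fewer minor events enter the formal comparison, so the test will have less power for them. They remain visible in the descriptive listing.
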